# 5. STUDY METHODOLOGY

# 5.1 IDENTIFICATION OF PARTICIPANTS

Potential participants will be identified by their healthcare team comprising of clinical nurse specialist or surgeon.

Potential participants who have previously been diagnosed with colorectal cancer will be identified through their attendance at out-patients clinic appointments, again by a member of the healthcare team.

# 5.2 RECRUITMENT OF PARTICIPANTS

Potential participants will be given a study information sheet by a member of the healthcare team either when they are on a surgical ward, or when they attend the surgical or oncology out-patients clinic for review.

They will be given appropriate time to read the information, ask questions and decide if they wish to participate. Should potential participants like more time to consider the study, they will be asked to contact the study coordinator once they have made that decision and an appointment will be made to recruit them.

The person recruiting participants will be either a member of the healthcare team or a research nurse from the dedicated research team.

Recruitment will take place in a private area or room within either the ward or clinic. The study will be discussed with participants and their questions and concerns will be addressed prior to gaining informed consent.

# 5.3 INFORMED CONSENT

Written informed consent will be obtained from all participants.

The person responsible for recruitment will explain the research ensuring that the participants have a full understanding of the purpose and nature of the research and what it involves.

The research team will ensure that anyone recruiting participants to this study will be fully trained in obtaining informed consent.

Approach and recruitment of participants within a period of less than 24 hours may sometimes be necessary. Potential participants will still be given time to consider the research before deciding whether or not they wish to participate.

Individuals who might not adequately understand verbal explanations or written information given in English, or who have special communication needs will be offered the appropriate support through the provision of study materials translated into the appropriate language, an interpreter or interpreter for the deaf.

Consent will be sought to keep limited personal data about participant’s longer term. Due to the genetic nature of the research, there is a small possibility that the research will produce information that may be of clinical importance to the patient or their families in the future. Included in the consent form is a clause which seeks participant’s explicit consent detailing whether they wish to be informed of relevant findings or not.

If participants indicate that they wish to be informed about future research findings which may be relevant to them, we will keep personal data relating to their name, address, general practitioner, next of kin or name of a blood relative.

# 5.4 PARTICIPATION IN OTHER TRIALS

Patients currently on clinical trials of treatment will not be recruited into this study.

# 5.5 CONCOMITANT MEDICATION

Patients currently on aspirin therapy or aspirin containing products will have this documented along with the dose and reason for prescription and any other prescribed or medicinal products being taken at the time of recruitment. Patients on already on vitamin D supplementation, or taking thiazide diuretics, digoxin or other cardiac glycosides, or anti-epileptic medication will be excluded.

# 5.6 LABORATORY SAMPLES

A blood sample will be taken into 2 lithium heparin tubes and 2 EDTA tubes by venepuncture (~30mls). The rectal biopsy will be taken into RNA preservative. If patients are required to undergo further endoscopy for clinical reasons, we will request a study biopsy to be taken during this. All samples will be anonymised through use of an identifying number and will be processed by the Wellcome Trust Clinical Research Facility (WTCRF), Western General Hospital, Edinburgh. The research team will make arrangements for the safe transport of samples to the WTCRF through the use of a pre-paid sealed transport system. Following 12 weeks of Vitamin D supplementation repeat blood (~30mls) and rectal biopsies will be taken.

# 5.7 VITAMIN D SUPPLEMENTATION

**Eligible participants in the intervention arm** will be supplied with pharmaceutical grade vitamin D capsules (total dose of 3200iu/ 80mcg per day). If participants show interest in study involvement but are unable or do not want to take vitamin D supplements, they can be recruited to ill undergo identical assessment to other study participants and provide samples to enable assessment for natural variation in serum vitamin D levels and gene expression.

**5.7.1 Vitamin D Supply**

Fultium-D3 800 IU Capsules will be provided by NHS Lothian Pharmacy

Manufactured by:
Jenson Pharmaceutical Services Ltd.
[name]
[name]
London
[name]

**5.7.2 Storage**

The product does not require any special temperature storage conditions.

**5.7.3 Summary of Product Characteristics**

The SmPC, last updated on 29th June 2013 will be referred to: http://www.medicines.org.uk/emc/medicine/25664/spc

# 5.8 DEMOGRAPHIC DATA

Any documented occurrence of bowel polyps will be recorded along with any pre-operative and / or post-operative treatment including any short or long course of radiotherapy, chemo-radiation, combination chemotherapy, mono-chemotherapy or palliative chemotherapy in participants with colorectal cancer.

# 5.9 QUICK GUIDE RECRUITMENT SCHEDULE

Please refer to page 14, Figure 1 – Quick Guide Recruitment Schedule.

# 5.10 ( Figure 1 ) QUICK GUIDE RECRUITMENT SCHEDULE

**Identification of Participant**

**↓**

**Eligibility criteria assessed including renal function and calcium level**

**↓**

**Participant approach**

**↓**

**Participant Information Leaflet**

**↓**

**Written Informed Consent**

**↓**

**Blood sample, 2 x lithium heparin, 2 x EDTA and rectal biopsy**

**↓**

**Vitamin D supplementation for 12 weeks**

**↓**

**Return to specific clinic**

**Blood sample, 4 x lithium heparin and rectal biopsy**

**↓**

**Close**

#

# 5.11 (Figure 2) QUICK GUIDE RECRUITMENT SCHEDULE – 18 WEEK PROTOCOL

**Identification of Patient**

**↓**

**Eligibility criteria assessed including renal function and calcium level**

**↓**

**Patient approach**

**↓**

**Patient Information Leaflet**

**↓**

**Written Informed Consent**

**↓**

**Blood sample, 2 x lithium heparin, 2 x EDTA and rectal biopsy**

**↓**

**6 week interval (no vitamin D supplementation)**

**↓**

**Blood sample, 4 x lithium heparin and rectal biopsy**

**↓**

**Vitamin D supplementation for 12 weeks**

**↓**

**Return to specific clinic (WTCRF)**

**Blood sample, 4 x lithium heparin, and rectal biopsy**

**↓**

**Close**

# 5.12 ( Figure 3 ) QUICK GUIDE RECRUITMENT SCHEDULE

**Single Sample Measurement**

**Identification of Participant**

**↓**

**Eligibility criteria assessed including renal function and calcium level**

**↓**

**Participant approach**

**↓**

**Participant Information Leaflet**

**↓**

**Written Informed Consent**

**↓**

**Blood sample, 2 x lithium heparin, 2 x EDTA and rectal biopsy**

**↓**

**Close**

# 6. POTENTIAL RISKS AND BENFITS OF PARTICIPATION

# 6.1 POTENTIAL RISKS

Study participants may experience mild discomfort or bruising from venepuncture. Where possible, arrangements will be made to have the samples drawn at the same time as other routine samples.

Study participants may experience mild discomfort from rigid sigmoidoscopy. Rectal biopsies are routinely taken during colorectal assessment by rigid sigmoidoscopy and where possible, research samples will be taken at the same time as routine assessment. In such cases, patients recruited into the study will consent to a further additional small biopsy of rectal tissue prior to the procedure. Rigid sigmoidoscopy and rectal biopsy is not associated with significant risk of harm. Major risks include perforation, haemorrhage or pelvic sepsis, with a negligible incidence of each of these.

There is the possibility that a participant/ participant’s family will be identified as potentially having a greater risk of developing colorectal cancer and this could increase anxiety. In this instance, the lead Physician/Surgeon coordinating their care will be contacted and advised that it would be appropriate to refer the family to the local genetics service. Arrangements have been put in place with the four Scottish Regional Genetic Centres to ensure that such referrals are streamlined and that families will be seen in a timely manner.

Vitamin D is currently widely available 'over the counter' as a dietary supplement with its benefits and safety profile being well documented. The European Food Safety Authority has reported a no observed adverse effect level of up to 10000iu/day in healthy young men with minimal sun exposure with an upper limit of 4000iu/day set in order to embrace other ages and genders, including pregnant women. The following medical conditions will be elicited and relevant patients excluded from the study:

- Kidney disease
- High levels of calcium in the blood
- Atherosclerosis
- Sarcoidosis
- Histoplasmosis
- Over-active parathyroid gland (hyperparathyroidism)
- Lymphoma

# 6.2 POTENTIAL BENEFITS

**Benefit from participation in medical research**

Individuals agreeing to participate may find contributing to this exciting study to be a very positive experience.

**Benefit from serum blood sampling**

A review of previous blood results may identify renal disease or high calcium levels that would preclude entry into the study but require further management. The participant and relevant health care professionals will be informed of these results. Blood sampling may also identify significant vitamin D deficiency which would require prolonged vitamin D supplementation following the completion of the study.

**Benefit from DNA analysis**

DNA analysis will be limited to genes of known relevance to colorectal cancer. Should any participant possess alleles known to significantly increase colorectal cancer risk, appropriate counselling and further investigation or surveillance will be arranged.

**Benefit from rigid sigmoidoscopy**

Repeat rectal is unlikely to offer limited benefit. There is a small miss-rate associated with rigid sigmoidoscopy, flexible sigmoidoscopy and colonoscopy. Given this, repeat rectal visualisation may identify previously missed pathology, yet given the relatively small numbers of participants, this is unlikely.

**Benefit from vitamin D supplementation**

Therapeutic benefit from study vitamin D supplementation will be limited given the short period over which vitamin D supplements will be given.

# 7. STATISTICAL ANALYSIS

# 7.1 SAMPLE SIZE

Due to the novel nature of this study and methodology, a convention power calculation was not possible. Using genes which have been shown to be of particular interest to the relationship between vitamin D and bowel cancer, our department has calculated the mean expression of these genes to be ~7.5 units on gene expression (HT-12 microarray) analysis. An analysis of 10 genes would require a significance level adjusted for the effect of multiple testing (hence p<0.005) and with a conventional power level set at 80%. The maximum standard deviation on expression data was 0.42. Assuming 1 standard deviation (i.e. more than twice the observed between subject variation the number of subjects required to detect a change of 4 units (approximately 1.5 fold) would be n=8 and 8 units (approximately 2 fold) would be n=5. Assuming 2 standard deviations (i.e. more than four times the observed between subject variation, the number of subjects required to detect a change of 4 units (approximately 1.5 fold) would be n=57 and 8 units (approximately 2 fold) would be n=18.

*In vitro* pilot work to date has demonstrated a 5-7 fold increase in the expression of one gene of particular interest in response to vitamin D treatment which supports the above calculations.

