# 3. STUDY DESIGN

# 3.1 STUDY OUTCOME MEASURES

PRIMARY OUTCOME – the change in expression of genes relevant to colorectal cancer risk in response to vitamin D supplementation.

SECONDARY OUTCOMES - the genotypic associations with changes in gene expression in response to vitamin D supplementation, the change in serum and tissue vitamin D level after vitamin D supplementation.

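### The only multiplicity level stated for the ten genes is p<0.005 (single-step Bonferroni); naming Holm's step-down rule would keep the same 5% family-wise control and gain some power (optional).

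*Protocol*

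**What the plan says.** Protocol section 7.1 (Sample size) sets the planning inputs for the gene expression analysis. On multiplicity it says: "An analysis of 10 genes would require a significance level adjusted for the effect of multiple testing (hence p<0.005". The same sentence continues "with a conventional power level set at 80" per cent. The sample sizes that follow (8, 5, 57 and 18) are presented as resting on that level.

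Section 7.2 (Methods of analysis) compares pre- and post-treatment expression with the Mann-Whitney U test. It gives no threshold and no multiplicity procedure.

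Section 3.1 defines the primary outcome as "the change in expression of genes relevant to colorectal cancer risk in response to vitamin D supplementation". The outcome is plural, but the section does not give the number or identity of the genes. The figure of ten appears only in 7.1.

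The protocol names neither Bonferroni nor Holm, and does not state the overall error rate or whether tests are two-sided.

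**The concern.** A reader looking for the decision rule finds one number, 0.005, and would probably hold each of the ten genes to it. That is valid, but Holm's procedure dominates it. Holm rejects every gene that the fixed 0.005 level rejects and sometimes more, with the same strong 5% family-wise control and no assumption about how the genes are correlated.

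The primary outcome asks which genes respond, and the ten were picked for their interest in the vitamin D and bowel cancer relationship, so more than one responder is plausible. In that case a fixed level for every gene would miss some true responders without strengthening the error guarantee.

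**Working it through.** **Inputs from the protocol (7.1):** 10 genes, per-gene level 0.005, power 80%, and n = 18 as one of the stated sample sizes.

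**Inputs assumed here, not in the protocol:** overall family-wise level 0.05, two-sided tests, a paired t test on the change, the number of genes that truly change, and the correlation between genes.

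**Step 1: reproduce the stated level.** 0.05/10 = 0.005, an exact match. With ten independent null genes the family-wise error is 1 − 0.995^10 = 0.0489, so the level does its job.

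**Step 2: Holm's thresholds.** Order the ten p-values. Compare the i-th smallest with 0.05/(10 − i + 1) and stop at the first failure. The thresholds are 0.0050, 0.0056, 0.0063, 0.0071, 0.0083, 0.0100, 0.0125, 0.0167, 0.0250 and 0.0500. None is below 0.005, so every gene with p ≤ 0.005 is still rejected. The first is exactly 0.005, so the chance of at least one rejection is identical under both rules. Both facts hold for any valid p-values, including those from a rank test.

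**Step 3: effect size for the power comparison.** Solving the noncentral t equation for n = 18 pairs, two-sided 0.005 and 80% power gives a standardised change of 0.974. This is set by the planning power and is not a protocol figure. The 7.1 text attaches n = 18 to 8 units with 2 standard deviations. If that is read as 8/2 = 4, the noncentrality is 4 × √18 ≈ 17 against a critical t of about 3.2. Power is then almost complete under either rule and the comparison is moot. The gain below therefore applies where per-gene power really is near the planned 80%.

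**Step 4: simulation of ten paired t tests, 18 pairs, standardised change 0.974, independent genes.**

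| Genes truly changed | Average power per changed gene, 0.005 for all → Holm | Chance of finding all changed genes |
|---|---|---|
| 1 | 80% → 80% | 80% → 80% |
| 3 | 80% → 82% | 51% → 56% |
| 5 | 80% → 85% | 33% → 46% |
| 10 | 80% → 95% | 11% → 73% |

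With between-gene correlation 0.6, average power under Holm is 82%, 84% and 91% for three, five and ten changed genes.

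**Step 5: sensitivity to n and effect.** With standardised change 1 and 18 pairs, average power goes from 0.824 to 0.869 (five changed) and from 0.825 to 0.965 (ten changed). With 57 pairs and standardised change 0.5 it goes from 0.797 to 0.836 and from 0.797 to 0.934. The pattern is the same.

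**Step 6: family-wise error.** It stays at or below 5% for both rules. Holm uses more of the allowance. With five genes changed and five null, the fixed level gives 1 − 0.995^5 = 2.5% for independent genes (2.3% to 2.7% across simulations), and Holm gives about 4.3% to 4.6%.

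**Step 7: what Holm cannot do.** With Mann-Whitney and 5 samples per time point, the smallest exact two-sided p is 2/C(10,5) = 2/252 = 0.0079. This exceeds 0.005, so neither rule could reject any gene at the stated n = 5.

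**The case against.** The strongest objection is that the quoted sentence contains no error. It sits in the sample-size section, is conditional in wording, and supplies an input to the power reasoning. Since 0.005 is also Holm's first threshold, planning at 0.005 is right under either rule and conservative for any one gene under Holm. The step-down choice often belongs in a statistical analysis plan, which is not shown, and nothing in the protocol rules Holm out. This stands, and it limits the point to an optional improvement.

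Three stronger readings are tempting, and the document does not support them:

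- A reader might infer that the primary analysis is bound to p<0.005 for every gene. Section 7.2 states no such rule, and section 3.1 does not fix ten genes. What can be said is that 0.005 is the only level the protocol states.
- A reader might infer that the large gain in finding every changed gene (11% to 73%) is what the study gives up. That figure needs all ten genes to respond. The protocol does not say how many are expected to, and the one pilot response it cites concerns a single gene. With one responder the gain is nil.
- A reader might infer that Holm costs nothing. Family-wise control at 5% is kept, but the realised error moves closer to 5%, and matching simultaneous confidence intervals are less simple than under Bonferroni.

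The power figures also assume a paired t test, whereas the protocol names Mann-Whitney. The ordering of the two rules does not depend on this, but the percentages do.

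**Conclusion.** The point holds as an optional efficiency gain. The protocol's only stated multiplicity level is a valid single-step Bonferroni level, and 7.2 adds no other rule. If that level is used for every gene, Holm would do at least as well in every case. Under the assumptions above (18 pairs, paired t, 80% power at 0.005, independent genes), the gain per truly changed gene is about 0, 2, 5 and 15 points with one, three, five and ten genes changed, and somewhat less at the upper end if genes are correlated. There is no failure of type I error control, no change in the chance of at least one finding, and no effect on the planned level.

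**What to change.** In section 7.1 keep p<0.005 as the planning level. In 7.1 or 7.2 add a sentence stating that the ten genes are tested by Holm's step-down procedure at a family-wise two-sided level of 0.05, with Holm-adjusted p-values reported. This also gives 7.2 an explicit decision rule. The cost is one sentence, with no added participants, samples or procedures. If simultaneous confidence intervals are wanted, say how they will be formed; intervals at the fixed 0.005 level remain valid but will not always match Holm's decisions.

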# 7.2 METHODS OF ANALYSIS

Serum vitamin D measurement will be undertaken by Liquid chromatography–mass spectrometry (Glasgow RI Biochemistry). Bowel tissue (rectal biopsy) measurement of vitamin D will be undertaken using a novel assay system reported in the literature (Immunodiagnostic Systems, Scottsdale, AZ, USA).

Genotyping will be undertaken to identify risk alleles using Illumina OmniExpress Exome GWAS arrays which provides comprehensive cost-efficient genotyping of loci of interest and pre and post active treatment gene expression assessed using Illumina HT-12 array and validated using qRT-PCR. Statistical comparison of pre- and post-treatment gene expression will be undertaken using the Mann-Whitney U test.

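### The n=5 scenario in Protocol 7.1 cannot reach two-sided p<0.005 with the Mann-Whitney U test fixed in 7.2, so the 80% power claimed for it is 0%

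*Protocol*

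**What the plan says.** Protocol 7.1 (Sample size) sets the planning threshold and power: "An analysis of 10 genes would require a significance level adjusted for the effect of multiple testing (hence p<0.005"), "with a conventional power level set at 80"%. It reports an observed variation ("The maximum standard deviation on expression data was 0.42") and then gives four scenarios.

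- First pair: "Assuming 1 standard deviation (i.e. more than twice the observed between subject variation"), the number needed to "detect a change of 4 units (approximately 1.5 fold) would be n=8 and 8 units (approximately 2 fold) would be n=5".
- Second pair: "Assuming 2 standard deviations (i.e. more than four times the observed between subject variation"), giving n=57 for 4 units and n=18 for 8 units.

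Section 7.1 names no test and no sidedness, and it does not pick one of the four figures as the target.

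Protocol 7.2 (Methods of analysis) names the test: the comparison of pre- and post-treatment expression "will be undertaken using the Mann-Whitney U test". Section 3.1 defines the primary outcome as a change in expression, without a direction. Section 5.6 and Figure 1 have the same participants biopsied before and after 12 weeks of supplementation.

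**The concern.** A rank test has a smallest attainable p-value that depends only on the number of observations. Once the two sets of values are completely separated, a larger effect cannot lower p any further. If that minimum lies above the significance threshold, the test cannot reject and its power is zero.

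Section 7.1 fixes a threshold and a sample size, and 7.2 fixes a test. In the n=5 scenario the three do not fit together. The four scenarios are the protocol's only sample-size justification, so one of them is offered as sufficient when, under the planned test, it could not yield a positive primary result for any gene at the stated threshold. Participants would have undergone two rectal biopsies for that.

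**Working it through.** **Inputs.** Threshold 0.05/10 = 0.005, strict inequality (7.1). Power 80% (7.1). Stated n: 8 and 5 (SD 1), 57 and 18 (SD 2) (7.1). Test: Mann-Whitney U (7.2). Assumption: two-sided, because 3.1 gives no direction.

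**Step 1: can the stated sizes be reproduced?** Reading 7.1 literally (4 or 8 units, SD 1 or 2), a two-sided paired t-test at 0.005 with 80% power gives:

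| Scenario | Standardised effect | Computed n | Stated n |
|---|---|---|---|
| 4 units, SD 1 | 4/1 = 4 | 5 | 8 |
| 8 units, SD 1 | 8/1 = 8 | 4 | 5 |
| 4 units, SD 2 | 4/2 = 2 | 8 | 57 |
| 8 units, SD 2 | 8/2 = 4 | 5 | 18 |

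The set is not reproduced. Standardised effects of 2, 4, 0.5 and 1 in the same test give 8, 5, 58 and 18 (n=57 has 79.8% power), which is very close. One-sided, those effects give 7, 4, 51 and 16, a worse match. The sizes therefore look like output of a two-sided paired t-test. This is an inference: the protocol states neither the test nor those effects.

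**Step 2: smallest p for the planned test.** With n pre and n post values completely separated, the exact two-sided Mann-Whitney minimum is 2/C(2n,n).

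| n | C(2n,n) | Two-sided minimum | One-sided minimum |
|---|---|---|---|
| 5 | 252 | 0.0079 | 0.0040 |
| 6 | 924 | 0.0022 | 0.0011 |
| 8 | 12870 | 0.00016 | 0.00008 |

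At n=5, 0.0079 > 0.005, so two-sided power is 0% at any effect size. A simulation with standardised shifts from 1 to 8 gave no rejections. At n=8 the threshold is attainable, and at 18 and 57 the minimum is negligible.

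The large-sample approximation does not rescue n=5. The standard deviation of U is √(5·5·11/12) = 4.787. Complete separation gives z = 12.5/4.787 = 2.611, p = 0.0090; with continuity correction z = 12/4.787 = 2.507, p = 0.0122.

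**Step 3: caution for the repair.** The data are paired, so the obvious rank-based replacement is the Wilcoxon signed-rank test. Its exact two-sided minimum is 2/2^n.

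| Pairs | Two-sided minimum | Below 0.005? |
|---|---|---|
| 5 | 2/32 = 0.0625 | no |
| 8 | 2/256 = 0.0078 | no |
| 9 | 2/512 = 0.0039 | yes |

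Nine complete pairs is the minimum for attainability, and only with exact p-values. The normal approximation at 9 pairs gives z = 22.5/√(9·10·19/24) = 22.5/8.441 = 2.666, p = 0.0077. Attainability is also not 80% power: at 9 pairs only a set of differences all in one direction would reject.

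**The case against.** **Sidedness is not stated.** This stands as a condition. One-sided, n=5 can reach 0.0040. The two-sided reading rests on the non-directional outcome and on the better match of the stated sizes to a two-sided calculation.

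**n=5 is only a scenario.** Also true. It is the most favourable of four, 7.1 itself says that a conventional calculation was not possible, and nothing provides for stopping at five. This lowers the severity. It does not remove the contradiction, since these scenarios are the only justification given.

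**The threshold appears only in the planning text.** Section 7.2 repeats no threshold, and a statistical analysis plan could set another. But p<0.005 is the only one the protocol gives, and the 80% claim is tied to it.

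**A reader might infer that n=8 also fails.** As the protocol stands, it does not. The planned Mann-Whitney test can reach 0.00016 at n=8. The failure there arises only under a signed-rank test that the protocol does not plan. Being attainable does not by itself confirm 80% power: simulated with independent pre and post values, two-sided Mann-Whitney power at n=8 is about 100% at a standardised shift of 4 (the literal inputs) and about 67% at a shift of 2.

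**Larger faults lie alongside.** An unpaired test on paired biopsies, and sizes that do not follow from their stated inputs, both require 7.1 to be redone. That is fair, but it does not guarantee that this limit would be noticed: changing only the test name would make the problem worse.

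**Conclusion.** The point holds for n=5 only. Under a two-sided Mann-Whitney test at p<0.005, the claimed 80% power is 0%, because the smallest possible p is 0.0079. This rests on one assumption, two-sided testing, and otherwise on the protocol's own threshold, test and n. It does not depend on effect size, on variance or on the correlation within pairs.

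The documents do not support concluding that the study as a whole has no power, that n=8 is unusable under the planned test, or that enrolment will stop at five. That the sizes were derived from a t-test is likely but not stated. Severity is moderate.

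**What to change.** In Protocol 7.1 and 7.2:

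1. State the sidedness and name one paired test for the pre/post comparison, for example a paired t-test on log2 differences, or the signed-rank test.
2. Recalculate all quoted sample sizes for that test at p<0.005, stating the SD of the within-person change that is assumed.
3. Remove n=5 as sufficient for any rank test. If signed-rank is chosen, remove n=8 too, and say that at least 9 complete pairs with exact p-values are needed for p<0.005 to be attainable, with the n for 80% power given separately.

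The cost is rewording and a short recalculation. If a rank test is kept, the smallest quoted sizes become less favourable. A paired t-test avoids this floor (power at n=5 is 94.8% for a standardised effect of 4, and at n=8 it is 88.6% for an effect of 2), but at such small n it relies on the differences being roughly normal.

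### The four sample sizes in Section 7.1 are mutually inconsistent, and n=57 and n=18 do not follow from changes of 4 and 8 units at an SD of 2

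*Protocol*

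**What the plan says.** Protocol Section 7.1 opens by saying that a conventional calculation could not be done, then supplies the elements of one.

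- **Baseline level:** the department "calculated the mean expression of these genes to be ~7.5 units on gene expression (HT-12 microarray) analysis".
- **Significance level:** "An analysis of 10 genes would require a significance level adjusted for the effect of multiple testing (hence p<0.005".
- **Power:** "with a conventional power level set at 80" per cent.
- **Observed variation:** "The maximum standard deviation on expression data was 0.42".
- **First scenario:** "Assuming 1 standard deviation (i.e. more than twice the observed between subject variation", where the number needed to "detect a change of 4 units (approximately 1.5 fold) would be n=8 and 8 units (approximately 2 fold) would be n=5".
- **Second scenario:** "Assuming 2 standard deviations (i.e. more than four times the observed between subject variation", where the number needed to "detect a change of 4 units (approximately 1.5 fold) would be n=57 and 8 units (approximately 2 fold) would be n=18".

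The section names no formula, sidedness, pairing or expression scale, and adopts none of the four numbers as the target. Section 7.2 plans a Mann-Whitney U test for the comparison before and after treatment.

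**The concern.** With the significance level and power fixed, the required n for a comparison of means depends only on the change divided by the SD. The four scenarios contain two with the same ratio, and these are given different sample sizes. Doubling the SD while keeping the change at 4 units also takes n from 8 to 57, far more than halving the effect should cost at these effect sizes.

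These are the only figures that justify the study's size for its primary outcome. If they are wrong, the protocol does not tell the reader what change the study can detect. The link from units to fold change also depends on whether the mean of about 7.5 is a raw or a log2 value. A change of 4 units means something very different on the two scales.

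**Working it through.** **Inputs (Section 7.1).** Alpha 0.005 (0.05/10 genes); power 80%; mean about 7.5; observed SD 0.42; changes of 4 and 8 units. The scenario SDs are read as 1 and 2 units, because 1/0.42 = 2.38 and 2/0.42 = 4.76 fit the descriptions of more than twice and more than four times the observed variation. Two-sided testing is my assumption.

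**Step 1: consistency, without any formula.** Standardised effect d = change/SD.

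- 4 units, SD 1: d = 4, stated n=8
- 8 units, SD 1: d = 8, stated n=5
- 4 units, SD 2: d = 2, stated n=57
- 8 units, SD 2: d = 4, stated n=18

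The first and last share d = 4 and must need the same n. They are given 8 and 18.

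**Step 2: attempt to reproduce the figures.** For a paired t-test, take the smallest n for which a noncentral t with n−1 degrees of freedom and noncentrality d√n exceeds the two-sided 0.005 critical value with probability at least 0.80. The second variant replaces the SD by SD×√2, the SD of a difference between uncorrelated measurements. The third is a two-sample t-test.

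| SD, change | Stated n | Paired t | Paired t, SD×√2 | Two-sample t, per group (total) |
|---|---|---|---|---|
| 1, 4 | 8 | 5 | 6 | 4 (8) |
| 1, 8 | 5 | 4 | 4 | 3 (6) |
| 2, 4 | 57 | 8 | 11 | 9 (18) |
| 2, 8 | 18 | 5 | 6 | 4 (8) |

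At SD 1, n=8 equals the two-sample total and n=5 is within one subject of two variants. At SD 2, nothing comes near 57 or 18. One-sided tests, alpha 0.05, normal approximations and a Mann-Whitney inflation (t-test n/0.955) did not give them either.

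**Step 3: what the printed numbers do correspond to.** The paired t-test gives n = 8, 5, 58 and 18 for d = 2, 4, 0.5 and 1 (n=57 at d = 0.5 gives 79.8% power). Those effects equal change/(2×SD²): 4/2, 8/2, 4/8 and 8/8. One possible explanation is that the variance of a difference was entered where its SD belongs. This is inference, since the protocol shows no formula. At SD 2, d = 0.5 and 1 are changes of 1 and 2 units.

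**Step 4: direction of the error on the inputs as printed.** Each stated n is at or above the paired-t requirement (8 against 5, 5 against 4, 57 against 8, 18 against 5). Paired-t power at the stated n exceeds 99.9% in all four scenarios.

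**Step 5: the fold labels.** On a raw scale, (7.5+4)/7.5 = 1.53 and (7.5+8)/7.5 = 2.07, so the labels agree with the stated mean. On a log2 scale, 4 and 8 units would be 2⁴ = 16-fold and 2⁸ = 256-fold, while 1.5- and 2-fold would be log2(1.5) = 0.585 and 1 unit.

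**Step 6: consequence if the values are log2 (an assumption).** Paired t, two-sided 0.005:

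| SD | True change | Stated n | Power | n for 80% |
|---|---|---|---|---|
| 1 | 1.5-fold | 8 | 6% | 43 |
| 1 | 2-fold | 5 | 7% | 18 |
| 2 | 1.5-fold | 57 | 25% | 160 |
| 2 | 2-fold | 18 | 18% | 58 |

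With the observed SD instead, the SD of change is 0.42×√(2(1−r)), where r is the within-person correlation (assumed 0 to 0.8). The required n then runs from 18 down to 7 for 1.5-fold and from 9 down to 5 for 2-fold. At r = 0, where the SD of change is 0.42×√2 = 0.59, n=18 gives 81% power for 1.5-fold.

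**Step 7: the planned test.** An exact Mann-Whitney test with five values before and five after has a smallest two-sided p of 2/252 = 0.0079. It cannot reach 0.005, so n=5 is not usable with the test in Section 7.2, whatever the effect.

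**The case against.** The strongest defence has four parts.

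1. **The protocol states no formula, so its figures cannot all be called wrong.** This stands for SD 1. A reader might infer that none of the four numbers is reproducible, but n=8 and n=5 match or lie close to standard variants. It does not rescue 57 and 18, nor the unequal n for equal standardised effects.
2. **The error is on the safe side.** This also stands for the inputs as printed. A reader might infer that the study is underpowered for 1.5- and 2-fold changes. That needs two conditions together: an unstated log2 scale, and SDs of 1 and 2 that the protocol presents as deliberate inflations. At the observed SD, 57 and 18 would be enough even on log2. Only n=8 for 1.5-fold and n=5 for 2-fold could fall short, depending on r.
3. **The SD is between-subject, but the inflation covers this.** This largely stands. With equal variances and non-negative correlation the SD of change is at most 0.59, below both 1 and 2. The within-person SD is still the right quantity for a before/after outcome and should be the one stated.
4. **The section calls itself unconventional, so the numbers are only indicative.** This carries little weight. The text gives alpha, power, SDs and required n, and then says that pilot work supports them.

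**Conclusion.** The point holds as an internal contradiction and an arithmetic error. The four sample sizes do not come from one calculation on the stated inputs. At SD 2, 57 and 18 stand where about 8 and 5 are needed by paired t, or 11 and 6 with SD×√2. This rests on reading the scenario SDs as 1 and 2 units, as the text's own multiples imply, and on two-sided 0.005 with 80% power. The contradiction between 8 and 18 at d = 4 does not depend on the choice of test or sidedness.

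The documents do not show a loss of power. The fold labels fit the stated mean on a raw scale, and there the printed numbers exceed what is needed. The powers of 6% to 25% are conditional on log2 values and the inflated SDs. What can be said without condition is that the scale, the formula and the working n are not declared, so the fold change the study can detect cannot be read from Section 7.1.

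**What to change.** Rewrite Section 7.1 as one calculation.

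- Declare the expression scale on which 7.5 and 0.42 were computed, and express the target change on that scale with its fold equivalent.
- Use the SD of the within-person change, 0.42×√(2(1−r)), over a stated range of r. The two untreated samples in the 18-week schedule (Section 5.11) could supply an estimate.
- State alpha 0.005, sidedness, 80% power and the test actually planned for the before/after comparison, so that Sections 7.1 and 7.2 agree.
- Correct the n values, name the n the study works to, and state the fold change that n detects.

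The cost is one paragraph. The correction does not require extra participants, but the stated detectable change may become less favourable, particularly if the values prove to be log2.
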